## Methods

The major aims of the study are as follows: (1) to identify barriers to implementing an integrated cardiovascular risk management program in families of individuals with a positive history of CHD, (2) to assess the effectiveness of an integrated cardiovascular risk management strategy (consisting of screening for risk factors, lifestyle education and linkage to primary care for cardiovascular risk factor management) on modifying risk factor clustering in families, and to assess changes in BP, lipids, glucose, haemoglobin A1c (HbA1c), smoking, diet and physical activity and (3) to estimate the scalability of the integrated cardiovascular risk reduction strategy in families of individuals with a positive history CHD for state- or nation-wide implementation.

The proposed project uses mixed methods to achieve the study aims. The three design approaches include: Aim 1, formative qualitative research; Aim 2, a randomized controlled trial; and Aim 3, cost effectiveness and evaluative qualitative research to inform acceptability and scalability.

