### Cost effectiveness and acceptability analyses (Aim 3)

The intervention costs will include the resource inputs (e.g., personnel salaries, and materials) that are required to deliver the intervention (in total and per participant). Direct and indirect costs incurred by each family will be estimated using questionnaires administered at study visits 0, 12 and 24. Questionnaires will capture direct medical costs, direct non-medical costs (travel), and indirect costs (missed work time, and lost productivity). To estimate the cost-effectiveness (cost per one count decrease in clustering of risk factors), the between trial group difference in intervention delivery and patient direct costs will be divided by the between group difference in clustering of risk factors or cardiovascular risk score: [costs treatment arm – costs standard arm]/[ΣΔ Primary outcome-Treatment arm] – [ΣΔ Primary outcome-usual care arm]. Similarly, incremental cost utility ratio will also be calculated using data from a 12 monthly health utility assessment. Quality adjusted life years (QALY) will be used as the measure of health utility. The acceptability of the interventions will be assessed through qualitative research. Semi-structured FGDs (4-6 each in men and women) and in-depth interviews with FCHW (6 interviews) will be used to gauge the acceptability of the interventions.

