To compare the cost-utility of the intervention to standard arm management, we propose to calculate an incremental cost/utility ratio [net costs to net utility: costs of intervention – costs of control/utility of intervention – utility of control]. To calculate utility, we will use 12-monthly health utility. The chosen measure of utility will be the closest option to a global measure, the quality adjusted life year (QALY], and is calculated as the sum of mean survival time [life years] x utility scores at 12 and 24 months [25]. Both 12 and 24-month costs per QALY will be reported. If the intervention is successful, the modeled long-term cost-utility of the intervention and usual care will be compared using Markov Chain Monte Carlo estimation techniques, controlling for age, gender, and risk factor prevalence under different plausible scenarios for how these may evolve over time [26]. Then it will be compared to reference points from the literature – e.g., ceiling ratios for costs per QALY that are less than three times gross domestic product (GDP) per capita [27, 28] that are considered cost-effective [29] (India’s 2013 GDP per capita was $3990; threshold: ≤$11,100 per QALY).

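### The long-term cost-utility model, and the ceiling comparison tied to it, are run only if the intervention is 'successful'

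*Protocol article*

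**What the plan says.** The cost-utility paragraph of the Data analysis plan in the protocol article sets the rule: "If the intervention is successful, the modeled long-term cost-utility of the intervention and usual care will be compared". The next sentence begins "Then it will be compared to reference points from the literature" and gives a ceiling per QALY based on gross domestic product per head. The pronoun is loose, but the natural reading is that it refers to the modelled long-term result, so the comparison inherits the condition. The article does not define success.

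The rest of the economic and acceptability work is unconditional:

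- In the same paragraph, ahead of the condition: "Both 12 and 24-month costs per QALY will be reported".
- In the Aim 3 section, a within-trial ratio: "To estimate the cost-effectiveness (cost per one count decrease in clustering of risk factors), the between trial group difference" in costs is divided by the difference in risk factor clustering or risk score.
- In the same section: "incremental cost utility ratio will also be calculated using data from a 12 monthly health utility assessment".
- Also there: "The acceptability of the interventions will be assessed through qualitative research".

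The opening of Methods gives the third aim as "to estimate the scalability of the integrated cardiovascular risk reduction strategy" for state-level or national roll-out, and describes the design for it as "Aim 3, cost effectiveness and evaluative qualitative research to inform acceptability and scalability".

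**The concern.** Whether a programme is worth its cost depends on the expected difference in cost and in effect, and on the uncertainty around both. A significance test, or any other success filter, does not answer that question. An effect that misses significance may still be worth paying for, or may clearly not be, and a payer can use either answer.

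The condition falls on the economic result closest to the scale-up decision. The Discussion of the article says that a study of two years is not powered for cardiovascular morbidity and mortality. The value of better risk factor control lies mainly in events after that horizon, so 12- and 24-month costs per QALY can capture only a small part of it. The long-term model is meant to supply the rest.

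The rule therefore has two effects. In a borderline or unfavourable trial there is no long-term figure. Across possible trials, the long-term figures that do get produced come only from the favourable ones.

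**Working it through.** **1. What is conditional and what is not**

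| Output | Conditional on success? |
|---|---|
| Cost per one-count decrease in clustering | No |
| Incremental cost-utility ratio; 12- and 24-month cost per QALY | No |
| Acceptability (qualitative) | No |
| Modelled long-term cost-utility | Yes |
| Comparison with the ceiling | Yes, as the sentence order reads |

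**2. The plan's own sample size**

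Inputs from Trial sample size and power: 45% against 55%, two-sided alpha 0.05, 90% power, intra-cluster correlation 0.20, two participants per family, 15% loss, 370 families (740 participants) per arm.

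- Independent participants: n = [1.96 × √(2 × 0.5 × 0.5) + 1.2816 × √(0.45 × 0.55 + 0.55 × 0.45)]² / 0.10² = 524 per arm.
- Design effect: 1 + (2 − 1) × 0.20 = 1.2, and 524 × 1.2 = 628.8, so 629.
- Loss: 629 / 0.85 = 740 per arm, 1480 in all.
- Power after 15% loss: 0.900.

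The stated design reproduces exactly.

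**3. How often the long-term result would be missing**

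Assumption: success means a significant primary result in favour of the intervention.

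- Effective number per arm: 740 × 0.85 / 1.2 = 524.
- SE = √[(0.45 × 0.55 + 0.55 × 0.45) / 524] = 0.0307, or 3.07 percentage points. It is held at this value for every true difference d.
- Observed difference needed: 1.96 × 3.07 = 6.02 points.
- P(success) = Φ(d/SE − 1.96).
- Mean estimate given success = d + SE × φ(1.96 − d/SE) / P(success).

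| True difference (points) | P(success) | Chance of no long-term result | Mean estimate given success (points) | Ratio to truth |
|---|---|---|---|---|
| 10 (design) | 0.902 | 10% | 10.59 | 1.06 |
| 8 | 0.740 | 26% | 9.35 | 1.17 |
| 5 | 0.370 | 63% | 8.14 | 1.63 |

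The 0.902 differs slightly from 0.900 because this SE uses the separate variances of the two arms, while the sample-size formula uses the pooled variance under the null.

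**4. Sensitivity to the meaning of success**

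Suppose success meant only that the point estimate favours the intervention. The cut-off is then zero.

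- True 5 points: P(success) = Φ(5/3.07) = 0.95, so a 5% chance of no long-term result, and a mean estimate about 7% high.
- True 10 points: overstatement under 0.1%.

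The size of the effect thus depends heavily on a definition that the article does not give.

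**The case against.** The strongest case on the other side is that extrapolating beyond the trial only once an effect has been shown is a staged choice, announced in advance, for a secondary economic analysis. It leaves the primary analysis, the sample size and the within-trial ratios untouched. The 12- and 24-month costs per QALY are in the same unit as the ceiling, so a reader could set them against it unaided. A fuller plan may also define success. All of this is true, and it keeps the point small. It does not remove it: any definition based on a favourable observed effect selects in the same direction, and the within-trial ratios do not supply the long-term value.

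Three stronger readings are tempting, and the article does not support them.

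- **Aim 3 as a whole goes unanswered, or rests on inflated effects.** The unconditional ratios and the acceptability work contradict this.
- **Cost per unit of effect would be understated by about 39%.** That figure is 1 − 5/8.14. It requires success to mean significance, a true effect half the design value, a fixed incremental cost, and the primary risk difference as the model input. The article says none of these. The ceiling is per QALY, and selection on the primary endpoint carries over to QALYs only as far as the two are correlated, which is not stated.
- **Deleting the condition would correct an inflated estimate.** It would not. In a successful trial the same estimate enters the model with or without the condition.

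**Conclusion.** The point holds in a limited form. The article makes the long-term cost-utility model, and the ceiling comparison that follows it, depend on success, and so withholds the result most relevant to scale-up after a borderline or unfavourable trial. The fault is selective production of one result; it is not an error in the within-trial economics.

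The chances of a missing result (10%, 26% and 63% at true differences of 10, 8 and 5 points) rest on reading success as a significant primary result and on the plan's own design assumptions. The 8- and 5-point values are illustrations and are not taken from the article. At the effect that the trial was designed for, the overstatement given success is about 6%, on the primary endpoint only. Severity is low.

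**What to change.** Delete the condition. Suitable wording would be: *Whatever the primary result, long-term cost-utility of the intervention and usual care will be modelled from the intention-to-treat estimates with their full uncertainty, and compared with the stated ceiling.*

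The change adds an answer where there would have been none and ends the selective production of the result. The costs and utilities are to be collected in any case, so the only price is analyst time for the planned model when the primary result is not favourable.

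### The printed cost-per-QALY threshold of $11,100 is not three times the printed GDP per capita of $3990, which would be $11,970

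*Protocol article*

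**What the plan says.** The last paragraph of the protocol's Data analysis plan deals with cost-utility. If the intervention is successful, long-term cost-utility will be modelled for both arms. The text continues: "Then it will be compared to reference points from the literature". The example given is "ceiling ratios for costs per QALY that are less than three times gross domestic product (GDP) per capita". A closing parenthesis puts numbers to that rule for India: "2013 GDP per capita was $3990; threshold: ≤$11,100 per QALY".

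The sentence therefore holds a rule (a multiple of three), an input ($3990) and a result ($11,100). No other section gives a GDP figure, a different multiple, a currency conversion or a price-year adjustment.

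**The concern.** A reader who applies the stated multiple to the stated GDP does not obtain the stated threshold. At least one printed number is therefore wrong, or the two come from different sources that the text does not identify.

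At stake is how the modelled cost per QALY under Aim 3 would be read. With both figures left in place, a ratio falling between them could be called cost-effective under the rule or not cost-effective under the printed number. The choice could then be made after the result is seen, which stating a threshold in advance is meant to prevent.

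**Working it through.** **Inputs, all from the cost-utility paragraph of the Data analysis plan**

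- Multiple: 3 ("ceiling ratios for costs per QALY that are less than three times gross domestic product (GDP) per capita")
- GDP per capita: $3990 ("2013 GDP per capita was $3990")
- Stated result: $11,100 ("threshold: ≤$11,100 per QALY")

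**Step 1. Try to reproduce the plan's figure.** Threshold = multiple × GDP per capita = 3 × 3990 = $11,970. The stated $11,100 is not reproduced.

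**Step 2. Size of the gap.** 11,970 − 11,100 = $870 per QALY. Relative to the rule-based figure this is 870 / 11,970 = 7.3%; relative to the printed figure it is 870 / 11,100 = 7.8%.

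**Step 3. Solve backwards.**

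- With the multiple held at 3, the printed threshold implies a GDP per capita of 11,100 / 3 = $3700 exactly.
- With GDP held at $3990, it implies a multiple of 11,100 / 3990 = 2.78.

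**Step 4. Test rounding.**

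| GDP per capita used | 3 × GDP |
|---|---|
| $3700 | $11,100 |
| $3900 | $11,700 |
| $3990 (as printed) | $11,970 |
| $4000 | $12,000 |

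Rounding $3990 down or up to the hundred gives $11,700 or $12,000. Rounding the product instead does not help: $11,970 to the nearest hundred is $12,000. If $11,100 were itself rounded to the nearest hundred, GDP would have to lie between 11,050 / 3 = $3683 and 11,150 / 3 = $3717, well below $3990.

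**Step 5. Which results are affected.** A cost per QALY below $11,100 passes by either figure, and one above $11,970 fails by either. Only the $870 band between them gives conflicting answers.

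**The case against.** The strongest reply is that little hangs on this number, and most of that reply stands. A reader might infer that $11,100 is the decision rule for cost-effectiveness and hence for scalability. The protocol does not say so. The ceiling is one example among literature reference points, and the comparison follows a modelling step that is conditional on success. The 12- and 24-month costs per QALY are simply to be reported. The section on cost effectiveness and acceptability also defines a separate ratio, cost per one-count decrease in risk factor clustering, which has no GDP ceiling. The abstract bases scalability on acceptability as well as on cost-effectiveness.

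The direction of the error is also fairly benign. If $3990 is right, the printed threshold is too strict by $870; if $3700 was the intended GDP, the printed threshold is correct. In neither case does $11,100 admit a result that a correctly applied rule would reject.

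A second reply is that $11,100 does lie below three times $3990, so the wording is literally satisfied. This fails, because the text labels $11,100 as the threshold itself and not as one of the values under it.

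It is also tempting to conclude that $11,970 must be the right figure. The document does not support that: the GDP value may be the wrong one, or both may be. The $3700 above is only solved backwards and is printed nowhere.

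Two further criticisms should not be added. The difference between a strict and a non-strict inequality has no practical effect on a continuous ratio. Currency basis and price year are details that an article may leave to the full protocol or analysis plan.

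**Conclusion.** The inconsistency is real and can be verified within one sentence: the rule and the printed GDP give $11,970 per QALY, the printed threshold is $11,100, and the gap is $870 (7.3% of $11,970). This rests on only two readings: that the multiple is three, and that $11,100 is meant as the ceiling that multiple produces. Both are explicit in the text.

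The consequence is confined to reading the conditional, modelled long-term cost-utility result against its only numerical benchmark, and only for a ratio between the two figures. A wider reading, in which this undermines the trial's main conclusions, is not supported, because neither figure enters the primary outcome, the sample size or the effectiveness analysis. It is a small but definite error that should be corrected.

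**What to change.** Check the GDP per capita figure against the source the authors used, then make the two numbers agree before results are known. If $3990 is confirmed, keep it and state the threshold as $11,970 per QALY. If $11,100 was intended, correct the GDP figure; under the three-times rule it would have to be $3700, and the source must support that. If neither figure is confirmed, replace both and show the multiplication. The cost is one source check and, in most cases, one corrected number; nothing in the design, data collection or effectiveness analysis changes.

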**Trial registration number:**

NCT02771873, registered in May 2016 (https://clinicaltrials.gov/ct2/show/results/NCT02771873)

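### The only cost-effectiveness ceiling given a value is tied to 2013 GDP, although the trial's costs very probably arise later; state the ceiling as a rule for the price year of the costs

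*Protocol article*

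**What the plan says.** The protocol article's Data analysis plan proposes an incremental cost-utility ratio, with cost per QALY reported at 12 and 24 months. If the intervention succeeds, a long-term model follows, and its result is set against outside benchmarks: "Then it will be compared to reference points from the literature – e.g., ceiling ratios for costs per QALY". The benchmark is described as "ceiling ratios for costs per QALY that are less than three times gross domestic product (GDP) per capita", and a parenthesis turns it into money: "2013 GDP per capita was $3990; threshold: ≤$11,100 per QALY".

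Two other places bear on timing. Under Trial registration number the article gives "NCT02771873, registered in May 2016". Under Cost effectiveness and acceptability analyses (Aim 3), family costs come from "questionnaires administered at study visits 0, 12 and 24". The article gives no calendar date for any visit and no price year for the costs.

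**The concern.** A threshold in dollars per QALY is meaningful only when the costs set against it are in comparable money. Here the article prints a year, a GDP figure and a dollar threshold, and the year is about three years before registration. The article speaks of the trial in the future tense, and follow-up runs for two years after randomization. An analyst who takes the printed number at face value would probably be comparing costs from around 2016 onwards with a ceiling built on the 2013 economy.

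At stake is how Aim 3 is read. Scalability is to be judged partly on cost-effectiveness. If dollar GDP per capita rose after 2013, the printed ceiling is stricter than the rule it is meant to express, and a programme that passes the rule could fail the number. The primary endpoint, the sample size and the Aim 2 analyses are not affected.

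**Working it through.** **Inputs from the protocol article**
- Rule: below 3 × GDP per capita (Data analysis plan).
- GDP per capita: $3990, for 2013 (same place).
- Printed ceiling: $11,100 per QALY (same place).
- Registration: May 2016 (Trial registration number).
- Cost collection: months 0, 12 and 24 (Aim 3 section).

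**Inputs assumed, not in the documents**
- Growth of dollar GDP per capita: 0%, 3%, 5% or 8% a year.
- Gap between 2013 and the price year of the costs: 3 years (2016) or 5 years (2018). The first takes costs at about the registration date, the second at two years after it.

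**Step 1: reproduce the printed ceiling.** Rule × input = 3 × 3990 = 11,970, which is not 11,100. The difference is 11,970 − 11,100 = 870, or 870 / 11,970 = 7.3%. Working backwards, 11,100 / 3 = 3700 and 11,100 / 3990 = 2.78. So the printed ceiling corresponds to a GDP per capita of $3700, or to a multiple of 2.78. Rounding does not explain the gap.

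**Step 2: carry the rule forward.** Ceiling in year 2013 + y = 3 × 3990 × (1 + g)^y.

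| Assumed growth g | y = 3 | y = 5 |
|---|---|---|
| 0% | 11,970 | 11,970 |
| 3% | 13,080 | 13,877 |
| 5% | 13,857 | 15,277 |
| 8% | 15,079 | 17,588 |

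**Step 3: separate the two effects.** Dating alone multiplies the ceiling by (1 + g)^y. For growth of 3% to 8% this is 1.09 to 1.26 over three years and 1.16 to 1.47 over five. The arithmetic gap contributes a further 11,970 / 11,100 = 1.078. Together, against the printed figure, the range runs from 11,970 / 11,100 = 1.08 (no growth) to 17,588 / 11,100 = 1.58 (8% for five years).

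**Step 4: what if $11,100 is the right figure and $3990 is not?** Then the base is 3 × 3700 = 11,100. The same assumptions give 11,100 at zero growth, 12,129 at 3% for three years, and 16,310 at 8% for five years. The dating effect is unchanged in relative terms, and the arithmetic gap disappears.

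**The case against.** The strongest reply has four parts.

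1. **The number is an illustration.** The article introduces the ceiling as an example of a literature benchmark, and the dollar figures sit in a parenthesis. Nothing makes $11,100 the sole decision value or bars updating it. This stands. Yet it is the only benchmark given a value, so it is the one a reader or analyst is likely to apply.

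2. **The mismatch is inferred.** No price year is stated, so costs might be expressed in 2013 prices. A condensed article may also leave price year, inflation adjustment and currency conversion to a fuller document. This also stands: silence on those matters, including market versus purchasing-power dollars, is no finding by itself. What remains is that the article did print a dated figure and a dollar threshold, and fixed them badly.

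3. **The ceiling belongs to the long-term model.** It is applied to the modelled result, and only if the intervention succeeds. The 12- and 24-month ratios are merely to be reported. This is correct and narrows the point. The model would still need a price year, and the article states none for comparison with the ceiling.

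4. **Growth rates and years are assumed.** Correct. In addition, growth in dollar GDP per capita mixes inflation, real growth and exchange-rate movement. Deflating costs to 2013 and moving the ceiling forward are therefore not interchangeable, and the table is no measure of a pure price-year error. It shows only how far the plan's own rule could move.

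A reader might infer that costs and ceiling definitely are in different price years and that the cost-effectiveness verdict is therefore distorted. The documents do not support that. They neither date the visits nor state a price year, and they do not tie the verdict to the printed figure.

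**Conclusion.** The point holds in a limited form. The one ceiling with a value rests on 2013 GDP, in a trial whose costs very probably arise later. If the printed number is used for the modelled cost per QALY, the comparison could mix years.

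The direction is conditional. The dating makes the ceiling too strict only if dollar GDP per capita rose after 2013; a fall would work the other way. The size cannot be derived from the documents. On the assumed 0% to 8% growth over 3 to 5 years, with $3990 taken as correct, three times GDP per capita lies between about $11,970 and $17,600, against $11,100 as printed.

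One part needs no assumption: $3990 and $11,100 disagree under the stated rule, by $870. A result between $11,100 and $11,970 would be classed differently by the rule and by the number. The documents do not show which figure is in error.

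Severity is low. Only the Aim 3 cost-utility conclusion is affected.

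**What to change.** Replace the fixed dollar amount with the plan's own rule: three times India's GDP per capita for the price year in which the costs are expressed. State that price year, bring all costs to it, and convert costs and GDP per capita to dollars on the same basis. If a dollar figure is kept as an illustration, label it as such with its year.

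In the same edit, reconcile $3990 with $11,100, by correcting whichever is wrong or explaining how the threshold was obtained.

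The cost is a sentence or two now and one look-up at analysis. No data collection, sample size or Aim 2 analysis changes.
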